
## 2. Study Materials and Methods

### 2.1. Hypothesis and Aim

We aim to assess the effects of probiotic supplementation on the faecal microbiome composition of infants of mothers with GDM. We hypothesize that probiotic supplementation with triple-strain Bifidobacteria, 1 × 10^9^ CFU of each (*Bifidobacterium breve* M-16V, *Bifidobacterium longum* subsp. *infantis* M-63, *Bifidobacterium longum* subsp. *longum* BB536), will reduce dysbiosis compared to that of the control group. This will be assessed as an increase in the abundance of beneficial bacteria (e.g., bifidobacteria) and a reduction in the abundance of pathogenic bacteria (e.g., gammaproteobacteria).

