### 2.10. Primary Outcome

Faecal microbiome composition will be estimated using 16S rRNA and shotgun sequencing. Baseline gut dysbiosis will be assessed at Timepoint 1 (T1: first week of life) by evaluating the ratio of beneficial to pathogenic bacteria, with reductions in dysbiosis measured at Timepoint 2 (T2: after four months of supplementation) in the probiotics group compared to the placebo group. The following variables will be analysed: (1) the presence or absence of specific species or pathways and clusters based on the unsupervised clustering of the gut microbial profile; (2) alpha diversity, richness, the abundance of particular species or pathways, and the differences in these numeric variables (treatment vs. baseline).

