### 2.17. Probiotic Protocol

Enrolled neonates will be supplemented with the freshly reconstituted contents of the allocated sachets every day, which will be continued till four months of age. The dry, lyophilized powder in the sachets will be reconstituted using the mums’ own milk (first choice) or sterile water for injection. The dose will be 3 × 10^9^ CFU/day (1 mL reconstituted solution twice daily). Supplementation will be temporarily withheld if vomiting, diarrhea, or abdominal distension is noted.

The manufacturer, Morinaga Milk Industry Co., Ltd., are not a sponsor and will only supply the probiotic and placebo free for the trial and are not involved in the design, conduct, analysis, and reporting of the trial.

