### 3.1. Faecal Sample Collection

Stool samples will be collected from the diaper at two time points in sterile containers from each infant. The first sample (T1) will be collected as soon as possible after birth/admission to the postnatal ward (week 1). The second sample (T2) will be collected at the age of 4 months. All the samples will be labelled, weighed, and stored at −80 °C. After completing recruitment, the samples will be shipped on dry ice to the laboratory for storage at −80 °C and analyses. Acidified samples (5-fold in 1% phosphoric acid) will be shipped on dry ice to the laboratory for SCFA analysis.

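### The primary outcome can credit recovered product organisms as reduced dysbiosis, because bifidobacteria are both the treatment and the named marker of benefit and no washout is stated

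*Protocol article*

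**What the plan says.** **Marker of benefit.** Section 2.1 gives the test of the hypothesis in two parts: "This will be assessed as an increase in the abundance of beneficial bacteria (e.g., bifidobacteria" and the like, together with "a reduction in the abundance of pathogenic bacteria (e.g., gammaproteobacteria" and the like. The same section describes the treatment as "probiotic supplementation with triple-strain Bifidobacteria": *B. breve*, *B. longum* subsp. *infantis* and *B. longum* subsp. *longum*.

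**Primary outcome.** Section 2.10 assesses dysbiosis at baseline "by evaluating the ratio of beneficial to pathogenic bacteria, with reductions in dysbiosis measured at Timepoint 2". It then lists the variables to be analysed: first "the presence or absence of specific species or pathways and clusters based on the unsupervised clustering of the gut microbial profile", and second "alpha diversity, richness, the abundance of particular species or pathways, and the differences in these numeric variables (treatment vs. baseline". No species is named and the administered ones are not set apart.

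**Timing.** Section 2.17 gives the sachet "every day, which will be continued till four months of age". Section 3.1 plans two stools per infant, the first in week 1, and adds: "The second sample (T2) will be collected at the age of 4 months". No interval off product is stated, and no later stool is planned.

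**Measurement.** Sections 3.6.1 to 3.6.4 measure sequenced DNA. Section 3.6.2 uses relative abundance. Section 3.6.4 gives normalised counts at species level, and sub-species information for *B. longum* only. Both *B. longum* sub-species of interest are in the product.

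**The concern.** The genus named as the marker of benefit is the genus in the sachet, and it is measured at the age when daily dosing ends. Sequencing counts DNA from live, dead and transiting organisms alike. The analysis described does not distinguish a product strain from a resident strain of the same species or sub-species.

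An infant whose own flora has not changed can therefore show more bifidobacteria, a newly present species and a higher beneficial-to-pathogenic ratio simply because the product was swallowed. The pathogen share is not independent evidence either, since added product reads shrink every other taxon's relative abundance. At stake is whether a positive result could be read as correction of dysbiosis, which the abstract gives as the primary objective, or only as recovery of the product.

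**Working it through.** The plan gives no figure for product recovery, so there is none to reproduce. The only inputs from the document are 30 infants per group (2.9) and a two-sided 0.05 level (3.7). Detection rates, natural carriage, resident shares, the product's share of reads and the SD of the log ratio are assumptions, shown as ranges. Throughout, the resident community is taken to be identical in both arms.

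**1. Presence or absence of a product species.** Suppose the species is detected in all 30 treated infants and in 30 − k placebo infants. The two-sided Fisher p-value is 2 × C(30,k)/C(60,k).

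| Placebo carriers | k | p |
|---|---|---|
| 15/30 | 15 | 0.000006 |
| 18/30 | 12 | 0.00012 |
| 24/30 | 6 | 2 × 593,775/50,063,860 = 0.024 |
| 25/30 | 5 | 2 × 142,506/5,461,512 = 0.052 |

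With incomplete detection, 27/30 against 18/30 gives p=0.015. If 80% of placebo infants carry the species naturally, significance needs 24 or fewer carriers among 30, which happens in about 57% of trials. With detection in 80–95% of treated and 10–40% of placebo infants, the chance of significance is 0.91 to above 0.99 (normal approximation for two proportions).

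**2. Beneficial-to-pathogenic ratio.** Let B and P be the resident beneficial and pathogenic shares, and f the share of four-month reads that are product. The observed ratio is [B(1 − f) + f] / [P(1 − f)]. Relative to B/P, this is a rise of 1 + f/[B(1 − f)].

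| f | B=30%, P=20% (true ratio 1.50) | B=50%, P=10% (true ratio 5.00) |
|---|---|---|
| 5% | 1.76 (1.18-fold) | 5.53 (1.11-fold) |
| 10% | 2.06 (1.37-fold) | 6.11 (1.22-fold) |
| 20% | 2.75 (1.83-fold) | 7.50 (1.50-fold) |

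With product reads removed, the ratio returns to 1.50 or 5.00.

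**3. Chance that the ratio differs significantly from this alone.** With 30 per arm, the chance of significance in favour of probiotic is about Φ(ln(fold)/(SD × √(2/30)) − 1.96). For B=30%, P=20%, f=10% and SD 1.0: ln 1.37 = 0.315, 0.315/0.258 = 1.22, and Φ(−0.74) = 0.23. With no effect this probability is 0.025.

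| f | B=30%, P=20%, SD 1.0 | B=30%, P=20%, SD 2.0 | B=50%, P=10%, SD 1.0 |
|---|---|---|---|
| 5% | 0.09 | 0.05 | 0.06 |
| 10% | 0.23 | 0.09 | 0.12 |
| 20% | 0.65 | 0.22 | 0.35 |

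**4. Plausible f from the dose alone.** The dose is 3 × 10^9 CFU/day (2.17). With no multiplication in the gut, f = 3e9/(3e9 + R), where R is an assumed resident output in cells per day. R of 3e10, 3e11 and 3e12 gives f of 9.1%, 1.0% and 0.1%. A share of 20% would need growth in the infant or a smaller resident output.

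**5. Dilution of pathogens.** The observed pathogen share is P(1 − f). At f=10% and P=20% it is 18%, a relative fall of 10% with no change in the resident community.

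**The case against.** - **Colonisation may be the purpose.** The aim in 2.1 is the effect of supplementation on faecal composition, and lasting colonisation by the administered strains would be a genuine effect. This stands. But DNA in a stool at the end of dosing cannot separate colonisation from transit, so the label attached to it matters.
- **The ratio barely moves at low product shares.** This stands. At about 5% of reads or less the chance of a false signal is small, so the ratio that 2.10 uses to assess dysbiosis is only modestly exposed.
- **Section 2.1 also asks for fewer pathogenic bacteria.** This stands as a limit, since more bifidobacteria alone does not meet the full hypothesis. Dilution can still supply a small apparent fall.
- **Section 2.10 does not name the product species as those tested.** This stands, so the Fisher figures are conditional on one being chosen. Nothing in 2.10 prevents that choice.
- **Other variables are less exposed.** Alpha diversity (the basis of the sample size), richness and unsupervised clusters need not shift in the product's favour.
- **Strain-level work may sit in a fuller document.** It may. The point here is the definition in 2.1 and 2.10, not missing pipeline detail.
- **Section 2.11 could be read as placing T2 four months after supplementation.** Sections 2.10 and 3.1 and the Figure 1 legend all place it at the end of the four-month course.

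A reader might infer that the species variables must come out positive. The 57% figure at 80% natural carriage, and p=0.052 against 25/30, rule that out. A reader might also infer that the stool is taken during dosing. The text supports only that it is taken at the age when daily dosing ends, with no washout stated.

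**Conclusion.** The concern holds in a limited form. As worded, 2.1 and 2.10 let recovery of the administered organisms count toward reduced dysbiosis without any change in the resident microbiota. The effect is strong for presence of a product species when detection in treated infants is near complete and natural carriage is low to moderate. It is small for the ratio unless product reaches roughly 10% of reads or more. These sizes rest on assumed detection, carriage, resident shares, product share and SD.

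The documents do not support saying that the whole primary outcome is invalid, or that a positive result would mean only product recovery. This is a worthwhile, inexpensive clarification of what the trial may conclude.

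**What to change.** 1. In 2.1 and 2.10, state that presence or abundance of the three administered (sub)species is a colonisation or adherence measure and is not by itself evidence of reduced dysbiosis.
2. Pre-specify, before four-month data are analysed, a sensitivity analysis of the ratio and species variables that excludes reads mapping to the product strains, using the planned shotgun data.
3. Report pathogenic taxa also relative to non-product reads, so that dilution does not count as a fall.
4. Show results with and without product reads side by side. Describe reduced dysbiosis beyond product recovery only where taxa not in the product support it, such as fewer gammaproteobacteria.

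Do not make the product-excluded ratio a pass/fail gate. Suppose placebo has 50% bifidobacteria and 10% pathogens (ratio 5), and treated infants have 50% product, 20% resident bifidobacteria and 5% pathogens (ratio 70/5 = 14). Without product reads the treated ratio is 20/5 = 4, below placebo although the pathogen share halved. Relative to non-product reads the pathogens are 5/50 = 10%, as in placebo. Neither view settles the question alone.

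**Cost:** wording and one extra mapping step; no new stool. Exclusion also removes closely related resident strains and truly colonising product strains, so the excluded ratio may be biased against the probiotic and must be read with the full result.

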### 2.11. Secondary Outcomes

Faecal short-chain fatty acids (SCFAs) and bile acids will be quantified in the first week of life (T1), and again four months after probiotic supplementation (T2). Growth parameters, including weight, length, and head circumference, will be assessed at 4 (T2), 12 (T3), and 24 (T4) months of age. Developmental parameters will be evaluated using the Ages and Stages Questionnaire (ASQ) and the ASQ-Social Emotional scale, 2nd version, at 4, 12, and 24 months of age.

### 2.12. Rationale for Continuing Probiotics for Four Months

The introduction of solid foods around four months of age is an important dietary event during infancy that causes profound shifts in the gut microbial composition towards a more adult-like state [24]. Hence, we decided to target the dysbiosis of infants of diabetic mothers, while they are still on an exclusively milk-based diet.

### 2.13. Rationale for Assessing Growth and Developmental Parameters

There is conflicting evidence in relation to the effects of probiotics on growth. A recent systematic review by our group showed that probiotic supplementation was associated with better short-term weight gain [25]. Probiotic supplementation had no effect on neurodevelopmental impairment. They recommended more adequately powered RCTs that focus on the growth and neurodevelopment of infants receiving probiotic [25]. Another systematic review comprising of 79 RCTs concluded that in otherwise healthy children aged 0–59 months, probiotics may have a small, but heterogenous effect on weight and height in low- and middle-income countries, but not in children from high-income countries [26]. In contrast, a different systematic review, where the mean duration of probiotic supplementation was 5.6 ± 2.84 months, found no significant effect on weight or height [27].

The gut microbiota–brain (GMB) axis influences brain development and function via immune signalling, the hypothalamo–pituitary axis (HPA), the vagus nerve, and neurotransmitters produced by gut bacteria and metabolites, such as SCFAs, tryptophan derivatives, and bile acids. A systematic review which included nine RCTs (n = 3026 participants) demonstrated no significant difference in neurocognitive outcomes in between those treated with probiotics or a placebo, except in a subgroup of patients who received probiotics for >6 months (2 RCTs, n = 451 participants) [28]. However, a specific microbial pattern has been shown to be associated with variable developmental outcomes. A recent report showed negative associations of gross motor development with the relative abundance of Klebsiella and improved gross and fine motor scores with Lactobacillus and Streptococcus abundance [29]. Similarly, another study reported that Turicibacter and Parabacteriodes were highly abundant in the below-median fine motor score group, while Collinsella, Caprococcus, Enterococcus, Fusobacterium, Holdemanella, Propionobacterium, Roseburia, Veilonella, Bifidobacteria, and Lactobacillus were more abundant in the above-median fine motor score group [30].

### 2.14. Safety Monitoring

This will be assessed by monitoring for abdominal distension, vomiting, and diarrhea, leading to the cessation of supplementation. The risk of probiotic sepsis is rare, as reported in a recent systematic review [31]. To the best of our knowledge, probiotic sepsis has not been reported in healthy full-term infants in the literature. Moreover, probiotic sepsis (with Bifidobacteria) is easy to detect with blood culture and treat with routine antibiotics like penicillin and vancomycin. Fatality due to probiotics in preterm infants has not been reported so far, except for two cases, including one where death was attributed to a contaminated probiotic product [31]. In the second case, it was unclear whether death was ‘associated with’ or ‘due to’ probiotic sepsis (https://www.fda.gov/safety/medical-product-safety-information/risk-invasive-disease-preterm-infants-given-probiotics-formulated-contain-live-bacteria-or-yeast; accessed on 23 September 2024).

The risk of probiotic sepsis and associated morbidity is minimised by the independent microbiological assessment of the probiotic under investigation, the ability to detect bifidobacteria in blood culture using our routine blood culture assessment, and the susceptibility of probiotic bacteria to prescribed antibiotics for late-onset sepsis.

Bi-weekly phone calls will be made by the research team to parents to enquire about any gastrointestinal adverse effects, such as the number of stools per day, difficulty in passing stool as the number of stools difficult to pass per day, and stool consistency recorded using a validated 5-point scale (1 = watery, 2 = runny, 3 = mushy soft, 4 = formed, and 5 = hard) provided in a pictorial representation to parents. The frequency of spitting-up/vomiting and flatulence episodes per day will be recorded on a categorical scale (1 time; 2–3 times; 4–6 times; >7 times). Categorical scales will also be used to assess the daily durations of crying or fussing (<10 min; 10–30 min; >30 min to 1 h; >1–2 h; >2–3 h; >3 h), sleeping (0–7, 8–12, 12–16, 16–20, 20–24 h), or the severity of spitting-up/vomiting (1 teaspoon or less; 1 tablespoon; 2 tablespoons; about half of the feeding; more than half of the feeding). Episodes of abdominal distension (present or absent) shall be recorded in a parent diary. All adverse events will be recorded and evaluated by the investigators for causality and severity. Adverse events will be considered as serious if they are life-threatening, cause permanent harm, or results in hospitalization. All other adverse events will be considered non-serious.

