### 2.3. Participants

Infants of mothers with GDM born at >35 weeks and admitted to a postnatal ward.

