### 2.15. Establishment of a Data and Safety Monitoring Committee (DSMC)

A Data and Safety Monitoring Committee (DSMC) will be established. The committee will have the required expertise in paediatrics, neonatology, and trial design, but will not be involved in the care of study participants and would have no competing interests. The committee will monitor all the outcomes from recruitment until four months of age. The DSMC will review and approve the study protocol and will review all serious adverse events as they occur. No interim analyses are planned, but the DSMC will reserve the right to conduct an interim analysis or advise suspension or the termination of ongoing enrolment to this study.

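### The closed definition of a serious adverse event leaves a prolonged birth stay, and important events managed without admission, outside the DSMC's review of events as they occur

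*Protocol article*

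**What the plan says.** Section 2.14 (Safety Monitoring) first sets the criteria for seriousness: "Adverse events will be considered as serious if they are life-threatening, cause permanent harm, or results in hospitalization". A separate sentence directly after it then closes the definition with a residual rule: "All other adverse events will be considered non-serious".

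On the handling of events in general, the same section says: "All adverse events will be recorded and evaluated by the investigators for causality and severity".

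Section 2.15 says that the DSMC "will review all serious adverse events as they occur". It also gives the committee a wider remit: "The committee will monitor all the outcomes from recruitment until four months of age". On formal looks at the data it says: "No interim analyses are planned, but the DSMC will reserve the right to conduct an interim analysis".

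Section 2.3 describes the participants: "Infants of mothers with GDM born at >35 weeks and admitted to a postnatal ward". Supplementation starts at birth (Section 2.7), and sachets go first to the ward staff and later to the parents (Section 2.16).

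For tolerability, Section 2.14 has the daily frequency of vomiting and flatulence "recorded on a categorical scale (1 time; 2–3 times; 4–6 times; >7 times". Sleep is banded as 0–7, 8–12, 12–16, 16–20 and 20–24 hours.

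**The concern.** The label *serious* does one specific job in this plan: it decides which events the DSMC sees as they happen. A gap in the definition is therefore a gap in prompt independent review.

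The gap falls where this population is first exposed. These newborns are already in hospital when they start a live bacterial product. An event in those first days that delays discharge does not cause an admission, because the infant is already admitted. Later, at home, an event can matter clinically and still be managed without admission. Unless such an event is also judged life-threatening or permanently harmful, the residual sentence makes it non-serious.

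At stake is the speed with which independent reviewers learn of a signal. The Discussion presents the trial as also evaluating the risk of probiotic sepsis, so prompt review of an event related to that risk should not depend on how one investigator reads the definition.

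**Working it through.** No arithmetic applies to the main point. The check sets the definition beside the DSMC trigger and asks where particular events would go.

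**Step 1: is the list open or closed?** Section 2.14 names three criteria: life-threatening, permanent harm, hospitalization. Its next sentence assigns everything else to non-serious, so the list is closed. The article contains no other definition of a serious event.

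**Step 2: what does the label control?** Under Section 2.15, review as events occur is stated for serious events. For other events, Section 2.14 states recording and evaluation by the investigators. The remit over all outcomes to four months carries no timing, and no interim analysis is planned.

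**Step 3: apply the rule.**

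| Event | Life-threatening? | Permanent harm? | Results in hospitalization? | Label by the written rule |
|---|---|---|---|---|
| Event on the postnatal ward that prolongs the birth stay and resolves | No | No | No, already an inpatient | Non-serious |
| Important event at home, managed without admission, that resolves | No | No | No | Non-serious |
| Study-strain bacteraemia found on the ward, treated and cleared | A judgement | No | No, already an inpatient | Depends on that judgement |
| Event after discharge that leads to admission | Any | Any | Yes | Serious |
| Fatal event | Naturally read as yes | Naturally read as yes | Any | Serious on a natural reading, though death is not named |

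The first two rows are non-serious by rule. The third becomes non-serious only if the investigator judges the infection not life-threatening. That judgement is not far-fetched, since Section 2.14 itself describes bifidobacterial sepsis as easy to detect and treatable with routine antibiotics.

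**Step 4: how many infants are exposed to the gap?** Section 2.9 plans 30 per group, 60 in total. All are enrolled as postnatal inpatients, so all 60 pass through the birth-stay window. The article gives no event rate, so an expected number of affected events cannot be calculated.

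**Step 5: the tolerability scales.**

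- Vomiting and flatulence frequency has categories 1, 2–3, 4–6 and more than 7. Counts of 0 and exactly 7 have no category.
- Sleep bands share the endpoints 12, 16 and 20 hours, so each of these values fits two bands. Values between 7 and 8 hours fit none.
- The crying scale in the same section is contiguous and begins below 10 minutes, so it covers zero. The other two therefore look like drafting slips.

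**The case against.** The strongest case on the other side has four parts.

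**The DSMC is not blind to these events.** It monitors all outcomes to four months and may call an interim analysis or advise suspension, and every adverse event is recorded and assessed by the investigators. This stands in part: the events are not lost. But the remit has no stated timing, so it softens the gap in prompt review without closing it.

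**Investigators would use common sense.** A reader might infer from the missing word that deaths are classed as non-serious. The documents do not support that, because a fatal event is naturally read as life-threatening or as permanent harm. A reader might equally infer that any study-strain bacteraemia on the ward escapes the definition. That goes too far as well, because it does so only if judged not life-threatening. This part stands for death and in part for bacteraemia. It does not help with a prolonged stay, which meets none of the three criteria on any natural reading.

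**The medically important category comes from outside the article.** The article cites no seriousness standard, so its absence contradicts nothing in the text. That is fair, and the category is offered here as a repair. The problem it repairs is internal: a closed list joined to a reporting trigger.

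**The scale faults are minor and separate.** This stands. A reader might infer that they damage a main tolerability comparison or the count in a table of serious events. The article describes neither, and the data form is not shown. An infant with no episodes might simply have the item left blank, although a blank could then not be told apart from a missing answer.

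The allowance for a condensed article does not remove the main point. The article has not left the definition to a fuller document; it states one and closes it.

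**Conclusion.** The concern holds in a limited form. By the stated rule, an event that prolongs the birth stay, or an important event managed without admission, is non-serious when it is neither life-threatening nor permanently harmful. It then has no stated prompt route to the DSMC, though it may arrive later. A treated study-strain bacteraemia could fall in this class if judged not life-threatening.

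The consequence is delayed independent review of a narrow class of events in a 60-infant trial. The sample size, randomization, primary outcome and planned analyses are untouched. The conclusion assumes that the definition is applied as printed and that no other route to the DSMC exists beyond those in Sections 2.14 and 2.15. The prolonged-stay limb is the firmest. Naming death is a matter of clarity, and the scale faults are real but editorial.

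**What to change.** In Section 2.14:

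1. Add prolongation of an existing hospitalization to the criteria.
2. Add other medically important events, with a positive sterile-site culture for a study strain as an example.
3. Name death explicitly, for clarity.
4. Reword the residual sentence so that only events meeting none of the full list are non-serious.

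Section 2.15 can stay as written, because its trigger will then pick up the wider list.

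As a secondary repair, code vomiting and flatulence frequency as 0; 1; 2–3; 4–6; 7 or more, and make the sleep bands contiguous and non-overlapping.

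The cost is protocol and case report form wording and a few more reports to the DSMC. No endpoint, sample size, treatment rule or analysis changes.
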